**Tier 1**	
**1A**	◼ High distress with current suicidal ideation, plans, or behaviors.
	◼ PHQ-9 score ≥ 15 with intense feelings of anger, panic, anxiety, desperation, loss of control, or hopelessness.
**1B**	◼ High distress that does not include suicidal ideation, plans, or behaviors.
	Or
	◼ Prior suicide attempts and PHQ-9 score of 10–14.
	◼ Intense feelings of anger, panic, anxiety, desperation, loss of control, or hopelessness.
	Or
	◼ The current problems make it challenging to function.
**Tier 2**	◼ No current suicidal ideation, plans, behaviors, or prior attempts and moderate distress.
	◼ PHQ-9 score of 10–14.
	Or
	◼ Issues relating to alcohol or drug use or eating.
	Or
	◼ The current problems make is somewhat difficult to function.
**Tier 3**	◼ Minimal to no distress

Due to ethical considerations by the researchers, a therapist will contact all nurses who complete the mISP screening, no matter tier designation, as completing the mISP indicates that the individual may have some level of concern about their mental health. Participants meeting the inclusion criteria will continue the study while those meeting the exclusion criteria will be thanked for their time and provided with applicable resources outside of the study as determined by the therapist.

The study will operate out of The Ohio State University. Participants are currently being recruited and enrolled; however, recruitment and data collection have not been completed, nor have results been generated. The first participant was enrolled on October 26, 2023.

### Randomization

A computerized randomization scheme using permuted block randomization with varying block sizes of 2 or 4 is being implemented. Nurses in each block are randomly allocated 1:1 to the MINDBODYSTRONG^©^ and mISP program or mISP alone. Randomization is not controlled by any of the variables of interest in the study.

To ensure allocation concealment, the study team’s statistician developed the randomization scheme using SAS statistical software and input the coding into the randomization module in REDCap. The statistician is not involved with recruitment nor determining participant eligibility. The remaining study team members, in addition to the participants, are not privy to the randomization scheme. Awareness to group allocation only occurs after randomization.

To avoid techniques from the MINDBODYSTRONG© program being used with the attentional control group, the therapist is blinded to the approach used in the MINDBODYSTRONG© program. The therapist is also blinded to participant group allocation.

### Instruments and measures

The measures are administered electronically by study personnel via the mISP and REDCap. The mISP is used to determine participant tier designation, study eligibility, and to facilitate anonymous messaging with the therapist. Because data cannot be linked over time in the mISP, the measures are collected again in REDCap at baseline, immediately after program completion at week 8, and again at months three, six, and 12. The objective of the study measures is to evaluate any changes in mental health over time and assess **participants’ experiences with the interventions.**

#### Demographics

Demographic information collected will include gender, age, position, zip code, current mental health treatment, years as a nurse, and years practicing direct patient care.

#### mISP questionnaire

The mISP will identify nurses with moderate to high-risk suicide [36] via an objective, on-line screening questionnaire. Upon completion of screening, the mISP immediately outputs a tier designation based on participant responses that is only viewable to the therapist. The questionnaire will assess for intense emotional distress such as depression, anxiety, panic, rage, hopelessness, desperation, and loss of control which have been linked to depression with suicidal ideation. The participants will also respond to questions indicating burnout, substance use, disordered eating behaviors, post-traumatic stress disorder, current suicidal thoughts, behaviors, and plans, and past suicide attempts. This questionnaire is only taken once and is used to determine tier designation and study eligibility.

#### Patient health questionnaire (PHQ-9)

Depression will be assessed through the PHQ-9 [37] which is included in the mISP. This tool has been widely used in studies and has strong Cronbach’s alpha is reported above .90. It is scored based on a 4-point Likert scale with results categorized into five groups. Responses of 0–4 are considered minimal depressive symptoms, 5–9 are considered mild depressive symptoms, 10–14 are considered moderate depressive symptoms, 15–19 are considered moderately severe depressive symptoms, and greater than 20 are considered severe depression symptoms.

#### Columbia suicide severity rating scale

Suicidal intent will be measured with the valid and reliable Columbia Suicide Severity Rating Scale [38]. This is a semi-structured list of yes or no questions intended to assess the severity of suicidal ideation and suicidal behaviors. Questions are divided into four constructs: suicidal ideation, intensity of suicidal ideation, suicidal behavior, and lethality. The suicidal lethality construct uses a subscale rather than yes or no questions to track actual lethality.

#### Generalized anxiety disorder scale (GAD-7)

The valid and reliable GAD-7 [39] will be used to assess anxiety. This tool uses a 4-point Likert scale to measure feelings and actions associated with anxiety in the prior two-week period. The GAD-7 is widely used in research and in the field of mental health with Cronbach’s alpha is typically reported above .85.

#### Single-item burnout question

The following non-proprietary, single-item burnout question will be used: “Overall, based on your definition of burnout, how would you rate your level of burnout?” In a study of 5,404 participants, including 1,769 providers and 1,380 registered nurses, Dolan and colleagues [40] found that the single-item measure had a correlation of 0.79, sensitivity of 83.2%, specificity of 87.4%, and AUC of 0.93 (p  =  0.004) when compared to proprietary Maslach Burnout Inventory Scale.

#### Primary care PTSD scan for DSM-5 (PC-PTSD-5)

The PC-PTSD-5 is a 5-item screening tool to assess for probable PTSD in a primary care setting [41]. The instrument first asks about exposure to traumatic event to establish criteria for PTSD before asking five yes or no questions regarding PTSD symptomology. Recent studies have found the scale helpful in screening nursing and medical staff exposed to COVID-19 [42–45].

#### Job satisfaction scale (JSS)

The JSS is a 7-item scale using a 5-point Likert scale to determine the extent of satisfaction one feels towards their job [46]. A higher score indicates a higher level of job satisfaction. Cronbach alphas are typically reported as .80 and above.

#### Personal beliefs scale

The 10-item Personal Beliefs Scale was derived from the valid and reliable 16-item Healthy Lifestyle Beliefs Scale [47] and taps cognitive beliefs about dealing with stress and handling life’s problems (e.g., “I know how to deal with things that bother me in a healthy way”; “I am sure I can handle my problems well”). The Personal Beliefs Scale uses a 5-point Likert scale ranging from 1 (*strongly disagree*) to 5 (*strongly agree*). Eight specialists established content validity of the scale, and Cronbach’s alpha has consistently exceeded 0.80.

#### Healthy lifestyle behaviors scale

The Healthy Lifestyle Behaviors scale is a 16-item measure that assess the degree of engagement with healthy lifestyle behaviors (e.g., making healthy food choices and exercising). It is scored on a 5-point Likert scale ranging from 1 (*strongly disagree*) to 5 (*strongly agree*) [48]. The Cronbach alphas are reported at .80 and above.

#### Modified social readjustment rating scale

The Social Readjustment Rating Scale is a 43-item scale that identifies the frequency of various life events over the prior 12 months. The scale is intended to provide a quantitative view of life events that required the subject to make psychological adjustments that have been associated with the timing of illness development [49]. This scale has been modified to 10 life events for this study to reduce participant burden.

#### Open-ended stressors question

There will be one previously tested open-ended, self-report question regarding stressors [25, 50, 51]. The question is “Please take a minute to let us know about anything that has been particularly stressful for you lately–death of a loved one, relationship break-up, academic stressors, family or money problems, difficulty with your living situation–or anything else that might be contributing to how you are feeling”.

#### Program evaluation questionnaires

Feedback will be gathered regarding the participants’ experiences with the interventions in terms of their helpfulness (S4, S5 Files). These questionnaires will also gather data on any additional treatment, such as therapy or medication, the nurses may have received since the beginning of the study.

#### MINDBODYSTRONG^©^ facilitator responses

Qualitative data will be collected from participants during scheduled facilitator sessions regarding the participants experience with MINDBODYSTRONG^©^ and their progression through the program (S6 File).

### Processes and interventions

#### mISP screening and referral program

Once the questionnaire is submitted by a participant, it is automatically scored and stratified into one of four tiers by the mISP program: 1A, 1B, 2, and 3. Tier 1A and 1B are both participants in high distress, or high risk, differentiated by any level of current suicidal ideation. Tier 2 are participants at moderate risk of suicidal ideation without a history of suicide attempt or any current suicidal ideation. Respondents who do not meet any of these criteria are considered low risk and designated tier 3.

The therapist is notified immediately when a questionnaire is available on the mISP platform. The notification tells the counselor the tier of the participant and includes access to the participant’s responses to the questionnaire. The therapist will engage with each participant with a detailed assessment and personalized response after reviewing the participant’s questionnaire. Tier 1A and 1B participants are responded to within 24 hours, tier 2 within 36 hours and tier 3 within 48 hours.

Participants can review the therapist’s response by logging back into the mISP platform. All participants, regardless of tier, are invited to continue interacting with the therapist. Additional responses from the participants are answered within 24 hours. If identified as having moderate to high risk of suicide, tier 1A or 1B, participants can further engage with the counselor through the mISP or over the phone for support and assistance finding mental health resources. When indicated, the therapist will direct the participant to contact 988, the crisis hotline number, and encourage the participant to use their insurance benefits and/or employee assistance program to obtain local treatment. The therapist will provide referrals and bridge high-risk participants into treatment.

#### MINDBODYSTRONG^©^

Digitized MINDBODYSTRONG^©^ is hosted on an Ohio State University eLearning website. Participants must create an account to access the learning materials. There is no limit on the number of times participants can access the learning materials. Participants are encouraged to complete one learning module per week and completion reminders are sent weekly via email with or without text (based on participant preference) for eight weeks. Learning modules are video recordings varying from 9 to 20 minutes in length. Table 2 provides further details concerning the weekly modules.

**Table 2 pone.0303425.t002:** MINDBODYSTRONG^©^ learning module topics by week.

	Topic (length of module in minutes)
**Week 1**	◼ Thinking, Feeling, and Behaving (20 mins)
**Week 2**	◼ Self-Esteem and Positive Thinking/Self-Talk (11 min)
**Week 3**	◼ Stress and Coping (18 min)
**Week 4**	◼ Problem Solving & Setting Goals (10 min)
**Week 5**	◼ Dealing with you Emotions in Healthy Ways through Positive Thinking and Effective Communication (15 min)
**Week 6**	◼ Coping with Stressful Situations and Valuable Sleep (9 min)
**Week 7**	◼ Pulling it All Together for a Healthy YOU! (9 min)
**Week 8 (optional)**	◼ Post-Traumatic Stress Disorder (16 min)

MINDBODYSTRONG^©^ is completed asynchronously by the participant over eight weeks. A trained MINDBODYSTRONG^©^ facilitator checks in with participants over the telephone at baseline at weeks three and five of the online program to reinforce key program concepts and assess whether participants are completing the weekly skills building activities. Participants are informed that total time commitment per week is about 45 minutes, including time to complete learning modules, skills building activities, and facilitator discussions.

### Data management

Collected data will be encrypted and stored on a secure server which is located at the institution of the first author. Only the PI, external collaborators, and key personnel will have access to the electronic data and de-identified data. Data shared between study sites will be done via a password protected computer and server.

No datasets were generated or analysed during the current study. Because data deals with sensitive mental health information, data will not be made publicly available to protect participant identities. Data requests can be made by contacting the primary author. The final dataset will be de-identified and coded using unique identifiers to preserve participant confidentiality prior to release for sharing. Even with de-identification, the possibility of deducing participants with unusual characteristics remains. Thus, the data and associated documentation will only be made available to users under a data sharing agreement that provides for: (1) a commitment to using the data only for research purposes and not to identify any individual participant; (2) a commitment to securing the data using appropriate computer technology; and (3) a commitment to destroying or returning the data after analyses are completed. Given all data will be collected online no hard copies of the data will be obtained.

### Data analysis

We will conduct intent-to-treat analyses. Descriptive statistics will be first used to examine variable distribution, identify any data abnormality such as outliers, and summarize sample characteristics, stratified by intervention and control groups. Appropriate data transformation will be performed if needed to achieve normality. For each outcome variable, mixed-effects linear regression modeling will be used to fit the outcome as a linear function of intervention, time, intervention dose, and their interactions. Generalized linear mixed-effects regression with appropriate link function will be used if data fail the normality assumption. From the model, we will obtain estimates on the between-group difference in the change of outcome measure from baseline at each follow-up time point and estimates on the dose effect of the completed sessions in the MINDBODYSTRONG^©^ program. The model will be further extended to adjust for covariates, examine nonlinear relationships, and explore the heterogeneity of intervention effects across subgroups.

The study has seven outcomes and four between-group comparisons of pre-post changes for each outcome. Therefore, multiple testing adjustment to keep the study-wide type I error rate under 0.05 will be employed. Missing data due to attrition at longitudinal follow-up is expected. We will examine the extent and pattern of missing data, and perform appropriate multiple imputation according to missing data mechanism. The mixed-effects regression modeling allows for missing at random. This analysis will be repeated with and without multiple imputation. If missing not at random exists, pattern mixture modeling will be used instead. Sensitivity analysis will be used to examine the robustness of study findings before vs. after multiple imputation or under pattern-mixture modeling. We will use SAS 9.4 for all quantitative analysis. We will conduct two-sided tests and use Bonferroni adjusted p-values < 0.007 for statistical significance to keep the study-vide type I error rate under 0.05. Due to the conservative nature of Bonferroni adjustment for multiple testing, we will conduct sensitivity analysis using other approaches (e.g., Hommel method) [52]. Regardless of statistical significance, we will report point estimates, their precision (e.g., 95% confidence intervals), and effect sizes.

Qualitative data from the open-ended stressors question will be analyzed through inductive reflexive thematic content analysis using a manual method (no software required) [53, 54].

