### Sample size and power analysis

A power analysis was conducted based on two-sample t-tests to compare pre- vs. postintervention means with two-tailed tests and a study-wide type I error rate of 5% to adjust for multiple comparisons from seven outcomes and four between-group pre-post comparisons per outcome. Given previous positive results with MINDBODYSTRONG©, yielding a large effect size of .98 requires a sample size of 30 (21 after accounting for 30% attrition), which would detect effects with 80%. However, given the untested nature of the electronic on-line version of MINDBODYSTRONG©, a medium effect of .5 was used to calculate a desired sample of 254, which would detect intervention effects on outcomes (depression, SI, burnout, anxiety, post-traumatic stress, healthy lifestyle beliefs, healthy lifestyle behaviors, and job satisfaction) with 80% power and study-wide type I error rate of 5%. With an expected 30% attrition, we will need a target recruitment of at least 364 nurses from the ANA to ensure an analytical sample size of 254.

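### The planned between-group comparison of change from baseline has no stated baseline adjustment, which is unbiased but gives up precision that the baseline data already collected could supply

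*Protocol article*

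**What the plan says.** Under Data analysis, the protocol article states that "mixed-effects linear regression modeling will be used to fit the outcome as a linear function of intervention, time, intervention dose, and their interactions". The quantity reported from that model is "estimates on the between-group difference in the change of outcome measure from baseline at each follow-up time point". The same section counts the comparisons: "The study has seven outcomes and four between-group comparisons of pre-post changes for each outcome".

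Baseline adjustment is not part of this first model. Covariates appear in the next step, without being named: "The model will be further extended to adjust for covariates, examine nonlinear relationships, and explore the heterogeneity of intervention effects across subgroups". The Randomization section adds that "Randomization is not controlled by any of the variables of interest in the study", so the design does not balance baseline severity by stratification.

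The Sample size and power analysis section bases power on two-sample t-tests and specifies "two-tailed tests and a study-wide type I error rate of 5% to adjust for multiple comparisons from seven outcomes and four between-group pre-post comparisons", the four being counted for every outcome. It uses an effect of 0.5, 80% power and 254 analysed participants (127 per arm), and recruits 364 to allow for 30% attrition. It does not say whether 0.5 is in SDs of the raw score or of the change. Study design, and Instruments and measures, say that the measures are taken in REDCap at baseline, week 8 and months 3, 6 and 12, and can be linked.

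**The concern.** When baseline is one of the repeated outcomes and the model has a free intervention main effect, the arms may differ in mean at baseline. The intervention-by-time contrast is then the difference between arms in mean change. Randomisation makes the true baseline means equal, and this model does not use that fact. It subtracts the whole observed baseline difference, although only a fraction rho of that difference is expected to carry through to follow-up.

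What is at stake is precision. The trial expects to lose 30% of participants and tests against a strict multiplicity threshold, so an avoidable increase in standard error is worth removing, particularly for outcomes with a weak baseline-to-follow-up correlation.

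A smaller matter is that the coding of time is not given. The two possible codings, a categorical visit factor and a single slope, would give very different week-8 estimates.

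**Working it through.** **Inputs.** From the document: effect 0.5, two-sided tests, 5% study-wide error, 7 outcomes × 4 contrasts = 28 tests, 127 analysed per arm, 30% attrition. Assumed, because not given: baseline-to-follow-up correlation rho of 0.3, 0.5 or 0.7; equal variances at baseline and follow-up; complete data on the 127 per arm.

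**The plan's own figure.** The per-test alpha is 0.05/28 = 0.001786. The normal approximation gives n per arm = 2(z₁₋α/₂ + z₀.₈)²/d² = 2 × 3.965²/0.25 = 125.8, so 126 per arm or 252 in total. The noncentral t gives 129 per arm (258). Both are close to 254. At 127 per arm and d = 0.5, t-test power is 79.4%. For recruitment, 127/0.7 = 181.4, so 182 per arm or 364. The stated sample size therefore reproduces with 28 tests.

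**Precision.** In units of the raw-score variance:
- variance of change = 2(1 − rho);
- variance adjusted for baseline (ANCOVA or common baseline mean) = 1 − rho²;
- ratio adjusted/change = (1 − rho²)/[2(1 − rho)] = (1 + rho)/2.

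The last two columns give two-sample t power at 127 per arm and alpha 0.001786, with d = 0.5 in raw-score SDs divided by the square root of each variance.

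| rho | Variance, change | Variance, adjusted | Ratio | Power, change | Power, adjusted |
|---|---|---|---|---|---|
| 0.3 | 1.40 | 0.91 | 0.65 | 58% | 84% |
| 0.5 | 1.00 | 0.75 | 0.75 | 79% | 92% |
| 0.7 | 0.60 | 0.51 | 0.85 | 98% | 99% |

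By the normal approximation, the total N for 80% power is 354 against 230 (rho 0.3), 252 against 190 (0.5) and 152 against 130 (0.7), change against adjusted.

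**If 0.5 is in change-score SDs.** The change analysis then has 79% power whatever rho is. Adjustment raises the standardised effect to 0.5/√[(1 + rho)/2] = 0.620, 0.577 and 0.542, and power to 96%, 92% and 88%.

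**At the other threshold.** Data analysis also says it will "use Bonferroni adjusted p-values < 0.007 for statistical significance". At 0.007 with d in raw-score SDs, power is 74%, 90% and 99% for change against 93%, 97% and over 99% adjusted. The gain is in the same direction but smaller.

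**Time coding, conditional only.** Take visits at 0, 1.84, 3, 6 and 12 months (mean 4.568) and a true difference of 0, 0.5, 0.5, 0.5, 0.5 SD. The least-squares slope is 2.284/88.05 = 0.0259 per month. The implied differences in change are 0.0259 × 1.84 = 0.05, then 0.08, 0.16 and 0.31. All four are the same slope multiplied by a constant, so they would be one test. A truly linear effect would show no such distortion, and with visit categorical the problem does not arise.

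**The case against.** The change-score contrast is valid under 1:1 randomisation, widely used, and consistent with the pre-post basis of the sample size. If 0.5 is in change-score SDs, the trial has about its planned power without adjustment. The 58% figure needs both a correlation of 0.3 and a raw-score SD, and the document gives neither. At rho 0.5 the raw-score reading also gives 79%, close to the plan. Lack of stratification is no defect with 364 participants. The later covariate extension might include the baseline score, and an article may leave named covariates to the full plan.

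Most of this stands. The loss is one of efficiency and its size is uncertain. What does not fall away is that the article itself fixes the reported contrast as plain change and places covariate adjustment after it. That is a stated choice, and at any rho below 1 a more precise one is available from the same data.

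A reader might go further and infer from "fit the outcome as a linear function of intervention, time, intervention dose, and their interactions" that time enters as a straight line, so that the week-8 effect would be badly wrong. The document does not support that. The phrase is the ordinary description of a linear model, and the two-level intervention factor stands in the same list. Estimates at each follow-up and four comparisons per outcome fit categorical visits better, since nobody would correct for four contrasts that are a single test. The nonlinear relationships left to the extension could concern time, but equally dose or covariates.

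**Conclusion.** The point holds as an efficiency point. On the natural reading the planned contrast leaves baseline means free, and its variance is 1/0.85 to 1/0.65 times that of the adjusted contrast, or about 18% to 54% larger for rho from 0.7 to 0.3 (33% at 0.5). The power gain from adjustment at 0.05/28 runs from about 1 to 26 percentage points if 0.5 is in raw-score SDs, and from about 9 to 17 points if it is in change-score SDs. These figures rest on an assumed rho, equal variances and complete data.

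Using change from baseline does not bias the randomised comparison. Whether the dose term affects the intervention contrast is a separate question that is not examined here. The fall from 0.50 to about 0.05 SD at week 8 is not a finding against the plan. It shows only why the coding of time should be written down.

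**What to change.** In the primary model for each outcome, do one of the following, and report the adjusted between-group difference at each of the four follow-up visits:

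- keep baseline as a response and constrain the arm means to be equal there (constrained longitudinal analysis); or
- model only the follow-up visits, with the outcome's own baseline score, by visit, as a covariate.

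The two should not be combined for the same measure. In particular, baseline PHQ-9 must not be entered as a covariate in a depression model where it is already a response.

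As a clarification, state that visit is a categorical factor. It would also help to say whether the planning effect of 0.5 is in raw-score or change-score SDs.

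The cost is wording in the analysis plan. The baseline measures are already collected in REDCap and linked to follow-up, and neither the sample size nor the visit schedule changes. The change should be made before outcome data are examined by arm.

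### The plan replaces its mixed model with pattern-mixture modelling on a condition the data cannot establish, and guarantees no check under missing not at random

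*Protocol article*

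**What the plan says.** The Data analysis section of the protocol article expects data to be lost through attrition during follow-up and describes five steps.

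- The team looks at how much is missing and in what pattern, and will "perform appropriate multiple imputation according to missing data mechanism".
- The mixed-effects model is described as accommodating data that are missing at random (MAR).
- That model is run both with and without multiple imputation.
- "If missing not at random exists, pattern mixture modeling will be used instead".
- Sensitivity analysis addresses the "robustness of study findings before vs. after multiple imputation or under pattern-mixture modeling".

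The Sample size and power analysis section gives the scale of the loss: "With an expected 30% attrition, we will need a target recruitment of at least 364 nurses", so that 254 remain for analysis.

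**The concern.** Two features of the stated rule are troublesome.

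First, the condition for switching is that data missing not at random (MNAR) exist. Inspecting who drops out, and when, can show that data are not missing completely at random. It cannot separate MAR from MNAR. Because the sentence says *instead*, the answer to an unanswerable question decides which model carries the inference.

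Second, if the team does not declare MNAR, the sensitivity sentence can be satisfied by the comparison before and after imputation alone, since pattern-mixture modelling is joined to it by *or*.

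This matters here because the expected loss is large, the outcomes include depression and suicidal ideation, and the demands differ by arm. The MINDBODYSTRONG section describes weekly modules, reminders, facilitator calls and about 45 minutes a week for that arm only. The Limitations section itself allows that those who complete the intervention may be the more motivated, and that some nurses may be unable or not ready to take part in the programme. Dropout related to unseen outcomes, and differing between arms, is therefore plausible.

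**Working it through.** **1. Scale of the missing data.** Inputs from Sample size and power analysis: effect 0.5 SD, 80% power, two-sided tests, seven outcomes by four comparisons. With alpha = 0.05/28 = 0.001786, the two-sample formula gives 252 in total (normal approximation) or 258 (t distribution), against the stated 254. Power at 127 per arm is 0.805 or 0.795. So 254 is reproduced closely enough. Attrition: 127/0.7 = 181.4, rounded up to 182 per arm, or 364. The plan expects to lose 364 − 254 = 110 participants. No figure in the article is disputed on this point.

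**2. Can the trigger be applied?** Under MAR, the unseen scores of dropouts follow the distribution predicted from what was observed. Under MNAR they do not. The two differ only in the unseen scores, so any observed dataset is compatible with both. No criterion in a fuller document could turn this into a rule based on observed outcomes.

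**3. What each branch guarantees.**

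| Judgement reached | Model used | MNAR check the text requires |
|---|---|---|
| MNAR not declared | MAR mixed model, with and without imputation | None: the *or* is satisfied by the imputation comparison |
| MNAR declared | Pattern-mixture model, replacing the mixed model | The MNAR model becomes the analysis itself |

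**4. Possible size of the bias.** Let d be the fraction lost in an arm and δ the amount (in SD, unfavourable direction) by which its dropouts fall short of the MAR prediction. The MAR mean for that arm is too favourable by d × δ. For the treatment difference,

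bias = d(I) × δ(I) − d(C) × δ(C), with I = intervention and C = control.

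With d = 0.30 in both arms this is 0.30 × [δ(I) − δ(C)]. The shifts are assumptions, not figures from the article. So is the use of 30% in each arm, since the article gives one overall figure.

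| δ(I) − δ(C), SD | Bias, SD | Share of 0.5 | True effect if the MAR analysis shows 0.50 |
|---|---|---|---|
| 0 | 0 | 0% | 0.50 |
| 0.25 | 0.075 | 15% | 0.425 |
| 0.50 | 0.15 | 30% | 0.35 |
| 0.75 | 0.225 | 45% | 0.275 |
| 1.00 | 0.30 | 60% | 0.20 |

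Equal shifts with equal attrition give no bias. Equal shifts of 0.25 to 1.0 SD with 40% lost on intervention and 20% on control give a bias of 0.20 × δ = 0.05 to 0.20 SD, so 0.50 becomes 0.45 to 0.30. With 20% and 40% the sign reverses and 0.50 becomes 0.55 to 0.70. The observed data would be the same whatever the shifts.

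**5. Does agreement with and without imputation help?** A simulation of 1,000 trials used 182 per arm, a baseline and one follow-up, and a true benefit of 0.50 SD. About 31% of the intervention arm was missing, with dropout depending on the unseen follow-up score. About 30% of controls were missing at random. The baseline-adjusted MAR analysis of observed scores averaged 0.674. Multiple imputation under the same MAR model also averaged 0.674. The mean absolute difference was 0.010 and the correlation 0.99. The two analyses agreed closely and shared a bias of 0.674 − 0.50 = 0.174 SD. This is one constructed setting in which imputation used the same variables as the analysis. It shows that agreement is no evidence against MNAR, not how large the bias will be in this trial.

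**The case against.** The strongest reply is that the plan does name an MNAR method, and that its sensitivity sentence carries no trigger. That is correct. A reader might infer that the plan has no MNAR analysis at all, and the text does not support that. What remains is that the method is conditional in one sentence and optional in the next.

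A second reply is that the article never says the imputation assumes MAR. Choosing it by mechanism leaves a narrow opening for imputation under MNAR. This also stands as a matter of wording. However, the text sets imputation against a separate MNAR route, so MAR is the natural reading, and any MNAR imputation would rest on the same undeterminable diagnosis.

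Third, imputation can draw on variables outside the outcome model, such as life events or additional treatment received. Agreement with and without it therefore bears on the conditioning set and the imputation model. It would be too strong to say that the comparison is worthless as a robustness check. It is uninformative about MNAR specifically.

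Fourth, a reader might infer that the model will be picked after treatment effects are seen, outcome by outcome. The article speaks only of inspecting missingness and does not say that the choice is made per outcome. Judgement may also draw on outside information, such as facilitator contacts. That makes the trigger subjective, but it does not make it verifiable.

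Fifth, the control arm is not without contact. Sample and setting has the study team call all eligible consenting nurses, and the mISP section lets every participant continue with the therapist, with telephone contact for the highest tiers. The burden differs, but the contrast is not all against nothing.

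Finally, the range of shifts, the tipping-point method and similar details may properly be left to the analysis plan. They are offered in the fix as examples. The fault lies in the rule that the article states.

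**Conclusion.** The point holds in a limited form. The article makes the analysis model depend on a state of affairs that observed data cannot establish, and has the alternative replace the mixed model. The only check certain to accompany the mixed model is, on the natural reading, made under MAR. With 30% attrition expected, no MNAR check is guaranteed.

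The size is illustrative: a bias of 0 to 0.30 SD against the planned 0.5 for an excess intervention-arm shift of 0 to 1 SD, with 30% lost in each arm. A reader might take the upper figure as a forecast. The documents do not support that: the shifts are assumed, attrition is not given by arm or time point, and the bias is zero when shifts and attrition are equal. These figures measure what an MNAR analysis would need to explore, not the effect of the disputed sentence itself.

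**What to change.** Name the MAR mixed model as the primary analysis for every outcome, whatever the missing-data pattern. Delete the words that make pattern-mixture modelling a substitute, and change the *or* in the sensitivity sentence so that it is always run beside the primary analysis. A suitable form is a delta-adjusted analysis reporting the tipping point. The shifts should be set in advance, separately by arm, and on a scale suited to each outcome; an SD shift does not carry over directly to yes/no measures such as the PC-PTSD-5 items. The comparison with and without multiple imputation can stay, with its missing-data assumption stated.

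The cost is a change of wording and additional sensitivity runs across the outcomes and four follow-up times, in SAS, which the article already names. No new data are needed. The article reports recruitment still under way and no results generated, so on its own account the change could be made before any results exist.
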